#### Sample size

The power and sample size determination is based on a preliminary RCT, which revealed a moderate effect reduction in the burden of caregiving and improvements in patients’ HF-related health status [15]. With the use of G*Power v.3.1.9.7 for repeated-measures ANOVA with α = 0.05, Cohen’s d = 0.25 (moderate effect size), a power of 80%, two groups with 5 measurements, and correlations among repeated measures (0.50), a *sample size of 86 family dyads* will be needed. Our power analyses performed by this study’s statistician indicate that this sample size is sensitive enough to detect a significant difference in the study outcomes with this repeated measure design [36].

Our biostatistician’s revised precision calculation for linear mixed model analysis was based on the effect size outcomes of our HF palliative care studies. To account for an expected 20% attrition (many due to HF-related deaths), eight additional families will be recruited for each group. The calculated sample size was 86 patients, with an additional n = 18 for the expected 20% attrition rate (total sample N = 208; 104 patients and 104 caregivers) for this study. In this analysis, the random and fixed effects and quarterly repeated measures also add power.

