#### Randomization

The consulting statistician will use computerized randomization to generate numbers for subject enrollment. Two separate randomization lists will be created: one for males and one for females. Families will then be randomly assigned to either the control or intervention group at a 1:1 ratio. The group assignments are placed in sealed envelopes according to sex. Our RCT design adheres to CONSORT standards and rigorous research procedures [30]. The study is designed to enhance both internal and external validity, making it suitable for detecting differences between groups in behavioral intervention trials [31].

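### The sample size paragraph claims 80% power with 86 dyads for a moderate Cohen's d of 0.25, but 0.25 is moderate only as Cohen's f (d = 0.50); for a true 0.25 SD difference 86 dyads give about 18% to 46% power

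*Protocol article*

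**What the plan says.** The Sample size section of the protocol article describes the calculation as follows.

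- Method: "With the use of G*Power v.3.1.9.7 for repeated-measures ANOVA with α = 0.05". It does not say whether the between-group, within-subject or interaction effect was powered.
- Effect size and design: Cohen's "d = 0.25 (moderate effect size), a power of 80%, two groups with 5 measurements".
- Correlation: "correlations among repeated measures (0.50").
- Result: a "sample size of 86 family dyads", raised to 104 dyads for 20% attrition.

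A second paragraph mentions a revised calculation for a linear mixed model. It gives no inputs for it and keeps 86. It closes: "In this analysis, the random and fixed effects and quarterly repeated measures also add power".

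The Randomization section gives 1:1 allocation. Data analysis for Aims 1 & 2 plans a mixed model with treatment, time and their interaction, and Bonferroni control of the overall error rate.

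**The concern.** The value 0.25 cannot be both a Cohen's d and moderate. On Cohen's benchmarks a medium d is 0.50, and 0.25 is the medium value of f, which is what this G*Power procedure takes. The difference is a factor of two in the group difference that the trial is said to detect.

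This is the only quantified power statement in the article, and Aims 1 and 2 rest on it. Taken literally, it says that the trial would detect a quarter of a standard deviation four times in five. A reader could then treat a null result as evidence against an effect that the trial would more often miss than find. The listed inputs also do not lead to 86 in an obvious way, so the reader cannot recover what was meant.

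**Working it through.** **Inputs.** From the Sample size section: alpha 0.05, 2 groups, m = 5 measurements, correlation rho = 0.50, effect 0.25, N = 86 dyads. From Randomization: 1:1. For two equal groups f = d/2, so d = 0.25 is f = 0.125, and f = 0.25 is d = 0.50.

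**Formulas** (noncentral F, in G*Power's parameterisation):

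- Between-group test: lambda = N f² m / [1 + (m − 1) rho], df 1 and N − 2.
- Interaction: lambda = N f² m / (1 − rho), df m − 1 and (N − 2)(m − 1). A nonsphericity value epsilon multiplies lambda and both df; it is 1 unless stated.

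**Step 1: try to reproduce 86.** Smallest even N for 80% power with the listed inputs:

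| Test | f = 0.25 | f = 0.125 |
|---|---|---|
| Between groups | 78 | 304 |
| Interaction, epsilon = 1 | 22 | 78 |

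None is 86. Two departures from the listed inputs do give it:

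- Between-group test, f = 0.25, three measurements: lambda = 86 × 0.0625 × 3 / 2 = 8.06, power 80.1%, N = 86. The article states five.
- Interaction, f = 0.125, five measurements: N = 84 at epsilon 0.90, 86 at 0.87 and 88 at 0.85. The article states no epsilon.

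**Step 2: power of 86 dyads if 0.25 is f.** Between groups: lambda = 86 × 0.0625 × 5 / 3 = 8.96, power 84.1%. With the same lambda, alpha 0.05/2 = 0.025 gives 76% and alpha 0.05/5 = 0.01 gives 64%.

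**Step 3: power of 86 dyads if the true difference is 0.25 SD.**

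- *Mean of five measurements.* lambda = 86 × 0.015625 × 5 / 3 = 2.24, power 31.6%. All 104 dyads give 37.1%.
- *Baseline-adjusted mean of four follow-ups.* Variance of the mean: (1 + 3 × 0.5)/4 = 0.625. Less 0.5² = 0.25 for baseline: 0.375. Standard error: √(0.375 × 4/86) = 0.132. Ratio: 0.25/0.132 = 1.89. Power is about 46% (47% by normal approximation).
- *Interaction, 0.25 SD at every follow-up and 0 at baseline.* The SD of (0, 0.25, 0.25, 0.25, 0.25) is 0.10, so f = 0.10/2 = 0.05. lambda = 86 × 0.0025 × 5 / 0.5 = 2.15, power 18.0%.

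**Step 4: what f means in follow-up differences.** An average of d = 0.50 over five visits, with no expected difference at baseline after randomisation, needs 0.50 × 5/4 = 0.625, about 0.63 SD at each follow-up. An interaction f of 0.125 needs the same: 0.125 × 2 / 0.4 = 0.625, where 0.4 is the SD of (0, 1, 1, 1, 1).

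**The case against.** The best defence is that this is a slip of notation. The section calls the effect moderate twice, once for the preliminary trial and once beside 0.25, and it names a procedure whose input is f. Read as f = 0.25, 86 dyads give 84% power and nothing about the conduct of the trial changes. That stands, and it limits the consequence. It does not rescue the sentence, because changing the letter alone still leaves 78 for the between-group test with five measurements.

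A second defence is that 86 may come from an input that a condensed article leaves out. This also stands in part. The effect tested is unnamed, and an epsilon of 0.87 gives 86 for an interaction at f = 0.125; even at epsilon 1 that test has 84.5% power at 86. But such an interaction corresponds to about 0.63 SD at each follow-up, so it does not support 80% power for a 0.25 SD difference either.

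Three stronger readings are tempting and go too far:

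- *The trial is too small and needs 304 dyads.* That holds only if the target really was d = 0.25 on the five-visit mean. The article's description of the effect as moderate points the other way.
- *The team entered three measurements.* The match is exact, but it is only an inference about where 86 came from.
- *The closing remark that repeated measures add power is double counting.* It follows the mixed-model paragraph and altered no number. No error in the sample size can be shown from it.

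**Conclusion.** The statement of 80% power with 86 dyads for d = 0.25 is wrong as written. For a true 0.25 SD difference, power is about 32%, 46% or 18%, depending on the test, and none of the three comes near 80%. If 0.25 was meant as f, the target is d = 0.50 and 86 dyads are enough at unadjusted alpha (84%).

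That the listed inputs do not give 86 is firm for the between-group test (78). It is less firm overall, because neither the effect tested nor an epsilon is given.

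These figures assume equal groups, correlation 0.50 between all pairs of visits and complete data on 86 dyads. It would also be wrong to take 84% as the trial's real power. That figure averages baseline into the group difference and ignores the planned Bonferroni control, which would lower it to 76% for two tests or 64% for five. Those test counts are illustrations; the article does not fix the number.

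**What to change.** Keep 104 dyads and rewrite the paragraph so that it:

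1. gives the effect size as f = 0.25 (d = 0.50 for two equal groups), if that was the value entered;
2. names the effect that was powered and every input, including epsilon if one was used, and reconciles 86 with five measurements;
3. says that the trial does not have 80% power for d = 0.25;
4. gives the detectable follow-up difference for the planned mixed model, noting that d = 0.50 averaged over five visits including baseline means about 0.63 SD at each follow-up;
5. says that the power is at alpha 0.05, before the Bonferroni control planned for Aims 1 and 2.

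The statistician should check d = 0.50 against the effects in the preliminary trial on which the section says the calculation rests. The change is to wording and needs no extra recruitment. Its cost is that the stated detectable effect becomes less favourable.

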## Methods/design

### Aims

The aims of this RCT are to test the outcomes of the **HF**-FamPAL**home**CARE bundled intervention, with patients and family caregivers (104 dyads) managing home supportive EOLPC for end-stage HF in rural WV. The specific aims and hypotheses, with outcome measures for this RCT, are listed in Table 1.

**Table 1 Tab1:** Specific Aims, Hypotheses, with the Outcome Measures for this RCT

**Primary Aims** are to test the outcomes of the **HF**-FamPAL**home**CARE bundled intervention, with patients and family caregivers managing home supportive EOLPC for end-stage HF in rural WV
**Aim 1:** Compared to the control group at 3, 6, 9 months, and 1-year follow-up:
***Hypothesis 1a.*** The patients in the intervention group will have higher scores on HF-related health quality-of-life measure and on the functional health well-being scale
***Hypothesis 1b.*** The family caregivers in the intervention group will have higher scores on the functional health well-being scale
**Aim 2:** Compared to the control group at 3, 6, 9 months, and 1-year follow-up:
***Hypothesis 2a.*** The patients in the intervention group will have (a) lower depression and anxiety scores and (b) higher numbers of signed EOL advance directives
***Hypothesis 2b.*** The family caregivers in the intervention group will have (a) lower depression and anxiety scores, (b) lower home caregiving burden scores, and (c) improved home HF EOLPC preparedness and improved home palliative care scores
**Secondary Aim** (Aim 3) is to assess the bundled intervention helpfulness, cost, and the plans for maintaining the sustainability of our faith community nurses and visiting volunteers engagement across rural WV
***Aim 3a.*** Compare the bundled intervention helpfulness questionnaire ratings by the patient, family caregiver intervention group participants, and the interventionists (faith community nurse and visiting volunteers). Determine the implementation cost of the **HF**-FamPAL**home**CARE bundle
***Aim 3b.*** Using focus group research, determine 10-year plans for sustaining the bundle implementation, maintaining rural volunteers and coordinating administrative aspects of the program

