### Data analyses

All the outcome measures have established discriminant or construct validity, internal consistency, reliability, and specificity. Each has been used with diverse populations, chronic illness patients, and HF families. These measures have been shown to distinguish clinically significant differences and are responsive to changes over time. These questionnaires were easily completed within 30 min. The sample demographics will be tabulated and reported.

#### Data analysis for Aims 1 & 2

Our experienced statistician will employ hierarchical generalized linear models with repeated measures to identify significant differences in outcomes between groups and to control for nested dyadic analysis [49]. The models will include fixed effects of treatment, time, and the treatment‒time interaction. Patient and family caregiver effects will be treated as random to account for dependence among repeated observations on the same subject as well as among subjects within the same family [37]. These models detect changes in outcome variables over time, differences between groups, and within-group differences over time. The SAS Proc MIXED procedure will be utilized. General linear modeling using linear contrasts of selected model parameters will test for significant differences. Point estimates and confidence intervals will be produced via contrasts and estimates of appropriate linear combinations of model parameters. The overall experimental error rate will be controlled via the Bonferroni procedure for multiple testing.

Multicollinearity among study variables will be determined and statistically controlled for in the data analysis. The number of mental health visits (for severe anxiety and depression) will be tracked for comparison between groups. To assess differences in HF EOLPC decisions, the number of family members and patients who sign an advance directive form, reveal a decision, or identify someone to help with HF EOLPC options will be recorded and reported. The proportion of patients signing an advance directive form will be used to evaluate the acceptability of EOLPC discussions. Subjects’ outcomes will be recorded at the time of death or 12 months postintervention, whichever comes first.

#### Data Analysis for Aim 3

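### The stated 80% power comes from a five-measurement calculation that counts baseline, and is not shown to apply to the group differences at 3, 6, 9 and 12 months that Table 1 names

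*Protocol article*

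**What the plan says.** The Sample size section describes a G*Power calculation "for repeated-measures ANOVA with α = 0.05", an effect entered as Cohen's "d = 0.25 (moderate effect size), a power of 80" percent, and "two groups with 5 measurements, and correlations among repeated measures (0.50"). The result is a "sample size of 86 family dyads". The total is then raised to 104 dyads "with an additional n = 18 for the expected 20% attrition rate". The same section mentions a revised calculation for a linear mixed model, without its inputs, and closes: "In this analysis, the random and fixed effects and quarterly repeated measures also add power".

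The section on data collection for Aims 1 and 2 places the five measurements at baseline and at 3, 6, 9 and 12 months. Table 1 frames the hypotheses of Aims 1 and 2 this way: "Compared to the control group at 3, 6, 9 months, and 1-year follow-up". The data analysis section for Aims 1 and 2 fits treatment, time and their interaction, and then states: "General linear modeling using linear contrasts of selected model parameters will test for significant differences". It does not say which contrasts those are. Bonferroni control is planned, with the number of tests not given.

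**The concern.** A repeated-measures power figure belongs to one particular statistic. If it is the group effect averaged over all measurements, it draws power from averaging, and a pre-treatment measurement with no expected difference dilutes the effect. If it is the group-by-time effect, it depends on an interaction effect size. Neither is the difference between groups at a named follow-up visit.

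The stake is how results are read. A non-significant difference at a visit would be taken to come from a comparison with an 80% chance of finding the design effect, when the chance may be well below that.

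**Working it through.** **Inputs.** From the Sample size section: alpha 0.05, effect 0.25, m = 5 measurements, correlation ρ = 0.50, N = 86 dyads (43 per arm at the stated 1:1 allocation), 104 recruited (52 per arm). Assumed: two-sided test, equal correlations, standardised outcomes with SD 1, and the same difference d at every post-baseline visit with none at baseline.

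**Step 1. Reproduce the 86.** With f as Cohen's f (d = 2f for two equal groups):
- Between-groups option: λ = N f² m / [1 + (m − 1)ρ], df 1 and N − 2.
- Group-by-time option: λ = N f² m / (1 − ρ), df m − 1 and (N − 2)(m − 1).

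| Reading of 0.25 | Option | N for 80% | Power at N = 86 |
|---|---|---|---|
| f = 0.25 | between groups, m = 5 | 78 | 84% |
| f = 0.25 | group by time, m = 5 | 22 | near 100% |
| d = 0.25 (f = 0.125) | between groups, m = 5 | 304 | 32% |
| d = 0.25 (f = 0.125) | group by time, m = 5 | 78 | 84% |

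Example, first row at N = 86: λ = 86 × 0.0625 × 5 / 3 = 8.96, power 0.841. Among the variants tried at ρ = 0.50 and 80% power, only the between-groups option with f = 0.25 and m = 3 returned 86 (power 0.801), and the protocol states five measurements.

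**Step 2. Power for the comparisons the plan could make,** on the favourable reading (f = 0.25, so d = 0.50), 43 per arm. Two-sample noncentral t with noncentrality (δ/√v) × √(43/2), where δ is the expected difference and v the variance of the quantity compared:

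| Comparison | δ | v | Power |
|---|---|---|---|
| One visit | 0.50 | 1 | 63% |
| Change from baseline to one visit | 0.50 | 2(1 − 0.5) = 1 | 63% |
| One visit, baseline as covariate | 0.50 | 1 − 0.25 = 0.75 | 75% |
| Five-measurement average, no baseline difference | 4 × 0.50 / 5 = 0.40 | (1 + 4 × 0.5)/5 = 0.60 | 66% |
| Average of months 3, 6, 9 and 12 | 0.50 | (1 + 3 × 0.5)/4 = 0.625 | 83% |
| Same, baseline as covariate | 0.50 | 0.625 − 0.25 = 0.375 | 96% |

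For the treatment-by-time test with profile (0, 0.5, 0.5, 0.5, 0.5), λ = (43/2) × 0.4 = 8.6 on 4 and 336 df, giving 63%.

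**Step 3. Variations.**
- One visit at Bonferroni 0.05/4 = 0.0125: 41% (55% with baseline as covariate).
- One visit with all 104 dyads analysed: 71%.
- 80% at one visit needs 64 per arm, 128 dyads, before attrition.
- Baseline dilution: an average difference of 0.50 over all five measurements needs 0.50 / 0.8 = 0.625 SD at each follow-up visit.

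**Step 4. Literal reading, d = 0.25.** One visit: 21%. Average of the four follow-up visits: about 31%, or 46% with baseline as covariate. Treatment by time with 0.25 at each follow-up visit: λ = 8.6 / 4 = 2.15, about 18%.

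**The case against.** Several points on the other side stand, and they limit what can be claimed.

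- **The option is not stated.** A reader might infer that the trial was sized on the group main effect, because with f = 0.25 only that option comes near 86. The documents do not support this as fact: the interaction option with d = 0.25 as printed comes equally near (78 in both cases). The word moderate favours f = 0.25 but does not settle it.
- **The 80% is not the power of the five-measurement average either.** With f = 0.25 carried by that average, 86 dyads give 84%.
- **The deciding contrast is open.** A reader might infer that the 80% applies to no test in the plan. That goes too far. The model contains a treatment effect, Table 1's list of times can be read as the follow-up schedule, and a contrast averaged over follow-up is compatible with the analysis text and has about 83% at d = 0.50.
- **Double counting is not shown.** A reader might take the closing remark that quarterly measures add power as counting the five measurements twice. It may refer to the mixed-model calculation, whose inputs are not given.
- **63% is one value in a range.** Baseline adjustment or fuller follow-up raises it; Bonferroni or the literal effect size lowers it.

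It can also be said that the choice of contrast belongs in an analysis plan that is not shown. That does not remove the point, because the protocol itself prints both the power figure and the hypotheses, and does not connect them.

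**Conclusion.** The point holds, as a mismatch between a stated figure and the stated hypotheses. The printed inputs do not give 86 on either near reading, and the 80% is not shown to apply to a group difference at 3, 6, 9 or 12 months. At d = 0.50, the chance of missing the effect at a given visit is about 37% unadjusted and 59% at 0.0125, against the 20% implied. None of the readings examined brings a single-visit comparison to 80% with 86 dyads.

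These figures rest on equal correlations of 0.50, a constant post-baseline effect, 43 complete dyads per arm, and one continuous outcome. They do not show that the trial as a whole is underpowered: a follow-up average would exceed 80% before multiplicity adjustment if d = 0.50, and would fall well short if d is truly 0.25.

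**What to change.** 1. In the data analysis section for Aims 1 and 2, name the deciding test for each continuous outcome as the treatment contrast averaged over months 3, 6, 9 and 12. Leave baseline out of the average and preferably use it as a covariate. Report the single-visit contrasts as supporting.
2. In the Sample size section, state whether 0.25 is f or d, which G*Power option was used and how many measurements were entered. Restate power for the named contrast at the alpha actually used. Before multiplicity, at 0.05 and 86 dyads, this is about 83% (96% with baseline as covariate) if d = 0.50, and about 31% (46%) if d = 0.25.
3. If visit-specific contrasts are to stay decisive, replace 80% with the per-visit figure.
4. Do not present the quarterly measurements as a gain beyond the five-measurement calculation unless the mixed-model calculation is shown and supports it.

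The cost is wording and a rerun of the power calculation, with no extra patients or data. The price is that single-visit results become supporting, or that the printed power becomes less favourable.

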### Design/methodology

This study uses a randomized controlled trial (RCT) design stratified by sex to determine the effectiveness and helpfulness of the **HF**-FamPAL**home**CARE bundled intervention (N = 208, 104 dyads: 104 patients and 104 family caregivers). The intervention group (52 dyads) will receive the intervention. The control group (52 dyads) will receive attention control consisting of education on general health topics that indirectly affect HF (e.g., vaccinations, handwashing). At the end of the 12-month completion period, each group received the content provided to the other group. See Fig. 1.

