## Limitations and alternatives

The population of West Virginia is 93% Caucasian, but we have successfully enrolled underrepresented minorities in past studies. We anticipate a 20% attrition rate, primarily due to HF-related deaths. In previous studies, few caregivers withdrew after patient death, indicating that they were able to contact study nurses. To increase enrollment, program brochures are distributed in local churches by lay ministers and faith community nurses. Additionally, healthcare providers involved in HF patient discharges or ER visits may refer families to the program. Finally, the West Virginia University (WVU) integrated data repository (IDR) will be used for enrollment, as it has proven helpful for screening patients with HF across WV counties in the PI’s previous trials.

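### The attrition allowance is given as both 16 and 18 extra dyads, and neither keeps the stated 86 dyads at the stated 20% attrition

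*Protocol article*

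**What the plan says.** All the figures are in the protocol article.

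- **Number required (Sample size).** After a repeated-measures ANOVA calculation, "a *sample size of 86 family dyads* will be needed".
- **Attrition rate.** It is 20% under Sample size and again under Limitations and alternatives: "We anticipate a 20% attrition rate, primarily due to HF-related deaths".
- **First allowance (Sample size).** "To account for an expected 20% attrition (many due to HF-related deaths), eight additional families will be recruited for each group".
- **Second allowance (Sample size, next sentence).** "The calculated sample size was 86 patients, with an additional n = 18 for the expected 20% attrition rate", leading to "total sample N = 208; 104 patients and 104 caregivers".
- **Group sizes (Design/methodology).** "The intervention group (52 dyads) will receive the intervention"; the control group is also 52 dyads.
- **Allocation (Randomization).** "Families will then be randomly assigned to either the control or intervention group at a 1:1 ratio".

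The abstract and the Aims section also use 104 dyads.

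**The concern.** Two consecutive sentences give different allowances for the same attrition. The unit does not explain the difference: each dyad has one patient and is randomised as a dyad, so 18 extra patients are 18 extra families.

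The required number, the attrition rate and the enrolment figure are also linked by arithmetic, and as printed they do not fit together. This matters because the trial follows patients with NYHA III and IV heart failure for 12 months and expects its losses to come mainly from deaths, so attrition is a central planning assumption. A later report that cites this section would have to choose between two allowances, and would imply that 86 dyads were protected against a 20% loss when they were not.

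**Working it through.** **Inputs** (protocol article): 86 dyads required; 20% attrition; 8 extra per group, or 18 extra in total; 104 dyads enrolled, 52 per group, 1:1; α = 0.05; effect size 0.25; 5 measurements; correlation 0.50; 80% power.

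**1. Reproducing the 104**
- 86 + 18 = 104, and 104/2 = 52 per group. This agrees with Design/methodology.
- The likely route is 86 × 1.20 = 103.2, rounded up to 104. The article shows no formula, so this is an inference.

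**2. The two allowances**
- Eight per group: 2 × 8 = 16; 86 + 16 = 102 dyads, 51 per group.
- Eighteen in total: 18/2 = 9 per group; 43 + 9 = 52 per group.

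**3. What each allowance preserves.** Dyads retained = enrolled × (1 − 0.20); largest loss that keeps 86 = 1 − 86/enrolled.

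| Enrolled | Retained at 20% loss | Largest loss that keeps 86 |
|---|---|---|
| 102 | 81.6 | 15.7% |
| 104 | 83.2 | 17.3% |
| 108 | 86.4 | 20.4% |

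The number needed is 86/(1 − 0.20) = 107.5, so 108 (54 per group), which is 22 extra dyads. Multiplying by 1.20 takes the 20% as a share of the 86, whereas attrition applies to those enrolled: 18 is 20.9% of 86 but 17.3% of 104.

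**4. Effect on power.** Between-groups F test in a repeated-measures ANOVA with two groups: noncentrality λ = f²·N·m / [1 + (m − 1)ρ], on 1 and N − 2 degrees of freedom. The article writes Cohen's d = 0.25; the table *assumes* that 0.25 is Cohen's f, with ρ = 0.50.

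| Measurements m | N | λ | Power |
|---|---|---|---|
| 5 | 78 | 8.13 | 80.4% |
| 5 | 83 | 8.65 | 82.8% |
| 5 | 86 | 8.96 | 84.1% |
| 3 | 83 | 7.78 | 78.7% |
| 3 | 86 | 8.06 | 80.1% |

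For example, with N = 83 and m = 5: λ = 0.0625 × 83 × 5 / (1 + 4 × 0.5) = 25.94/3 = 8.65.

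With the five measurements stated, 80% power is reached at 78 dyads, not 86. The 86 reproduces with three measurements. So the cost of falling from 86 to 83 depends on which calculation produced the 86. If 0.25 is Cohen's d as written (f = 0.125), the same test needs about 304 dyads, and the gap between 83 and 86 is not what decides the power.

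**The case against.** The strongest reply is that this is a clerical slip with little consequence.

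- **The enrolment target is clear.** The abstract, Aims, Design/methodology and Sample size sections all give 104 dyads, and the design section gives 52 per group. This stands. A reader might infer from the word eight that recruitment would stop at 51 per arm. The documents do not support that: eight is the outlier, and the very next sentence gives 18 and 104.
- **The 86 is never called a number of completers.** This is also correct. Reading it as the number to be left after attrition is an inference, though a natural one, because the article adds dyads to it expressly to offset attrition.
- **A lost dyad still contributes data.** The analysis is a mixed model with repeated measures under intention to treat, outcomes are recorded up to death or 12 months, and the limitations section says few caregivers withdrew after patient death in earlier studies. So 83 counts complete dyads and is not the number analysed. This softens the effect but does not correct the allowance, which the protocol chose to make. The remark that random effects and repeated measures add power carries no figure.
- **Power hardly moves.** This holds if 0.25 is Cohen's f with five measurements. It is less comfortable if the 86 came from three measurements, where 83 falls just under 80%.

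That an article condenses the full protocol explains omissions, but not two conflicting figures.

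**Conclusion.** The point holds as an error in the stated sample-size arithmetic. The allowance of eight per group contradicts the 18 in total and the 52 per group, by two dyads overall. At 20% attrition, 104 dyads leave about 83 complete dyads, some three below the stated 86. Four more dyads (108) would be needed to keep 86, and 104 covers a loss of up to 17.3%.

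A reader might go further and conclude that the trial is under-powered because of this. The documents do not support that. The change is from about 84% to 83% on the f = 0.25, five-measurement reading, and from 80.1% to about 78.7% on the three-measurement reading. Both treat a lost dyad as contributing nothing, which overstates the loss under the planned mixed model. These power figures depend on reading 0.25 as f although the text says d, so the metric has to be settled before any power for 83 is quoted.

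**What to change.** Keep 104 dyads, 52 per group, and correct the Sample size section:

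1. Replace the allowance of eight families per group with nine per group, 18 in total.
2. State that at 20% attrition about 83 complete dyads are expected, and that 86 are kept only up to a loss of 17.3%.
3. Give the power for 83 dyads, naming the effect-size metric (f or d) and the number of measurements used, so that the figure can be reproduced.
4. If the authors rely on the mixed model's use of partial data, say so beside that figure.

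This changes wording and needs one recalculation. Enrolment, design and analysis stay as they are. The only concession is that the text no longer implies that 86 dyads are protected against a 20% loss.
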